### Analysis outline

Primary outcome in the quantitative study will be increased confidence in providing help in situations where people are in a mental health crisis or experiencing a mental health problem by comparing the intervention group after having attended the training course with the control group. Secondary outcome will be increase in knowledge about mental health problems and crisis and options for professional reference as well as an increase in positive attitudes towards people suffering from mental health problems also by comparison of the two groups. Power analysis was performed using PS – Power and Sample Size Calculation. We calculated that with alpha = 0.05, a power of 0.8 and a standard deviation 0.75, and a smallest clinically relevant difference in means between the groups of 0.19 we would require 250 persons per group.

Continuous outcome measures will be analyzed using generalized linear models including treatment allocation, test of interaction term between allocation and the vignette used, as well as variables associated with attrition or baseline imbalances between the groups, if any. Missing data is expected to be missing at random and handled using multiple imputations. Dichotomous outcome measures will be analyzed using binary logistic regression in the same manner. To describe the reliability of the data from the attitudes questions: “What you think” contra “what others think”, we will analyse by using Cronbach’s Alpha. The case and knowledge based items in the questionnaire will be ranked where high scores equal right answers. Data will be analysed using IBM SPSS version 22.

To take a systematic view on the qualitative data, we plan to use the software program Nvivo, which provide for a readily accessible categorizing and coding of the data. We will analyze the qualitative data using a phenomenological approach [17]. Here we will employ an emphasis on the structure of experience and consciousness centered on gaining knowledge and changing behavior. Based in phenomenology, the analysis will explore how knowledge and attitudes are produced and reproduced in ‘natural’ social situations. The analysis will thus be embedded in a perspective on the participants as a social group in an intersubjective life world. Thus, the analysis will both contain a characteristic of the participants as a social group, and an analysis of behavior and attitude. Lastly, the analysis of the qualitative data will present thoughts on contents of the educational programme.

Each set of data is independent, but provides a united understanding of the training program MHFA in a Danish context.

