## Methods/Design

The design of the study will combine concurrent and sequential elements within a mixed-methods convergent parallel design [16]. This choice of design is based on the nature of the objective of the research being both exploratory and confirmatory at the same time [17]. In the study, qualitative and quantitative data will be collected.

The design of the quantitative part is a randomized, waitlist-controlled superiority trial, in which 500 participants will be allocated to either the intervention group or the control group. The control group will attend the course 6 months later, hence waiting list design. From fall 2013 to spring 2014 participants will be educated “First Aid-helpers” following a manualized, two days MHFA course. All the participants will answer a questionnaire at baseline and at six months follow-up. Concurrently, the trial will be complemented by a qualitative study, in which five focus groups will be held with participants before and after they attend the course and participant observation will be carried out on the course.

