### Survey procedure

A link to the electronic questionnaires will be sent out at baseline and at six-month follow-up by email to the participants, primarily to their work email-address, in order to avoid loss to follow-up [14]. Reminders to complete questionnaires will be provided at both baseline and at follow-up.

The software program used for the distribution of the questionnaires will be Survey Xact [19].

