## Discussion

### Strengths and limitations

The randomization procedure offers strengths to this study by reducing the risk of selection bias. Equally, the analysis of the quantitative survey will be blinded with the intent of being unbiased.

The mixed-methods approach in the design of the study will allow us to qualify and further develop the results, and thereby present a more thorough evaluation of the MHFA training. The qualitative type of data gives greater depth, while the quantitative data gives greater breadth; together it yields results from which one can make better inferences [17].

The study may have some limitations. There can appear a risk of contamination between the intervention group and control group, since they will sometimes work at the same workplace. Previous studies have emphasized difficulties in obtaining adequate follow-up rates. However, in this study contacts are mainly on email, hopefully to prevent attrition bias, and missing data will be handled using appropriate statistical methods.

Furthermore, the study population represents a great part of people already working as ‘care takers’, which means that they may be especially motivated and already in line with providing help.

A limitation in the study can be that outcomes measured are sensitive to interpretation, hence a challenge to uniform. We hope that our use of a mixed-methods design in the study can strengthen the analysis and take up this challenge. In the evaluation study the quantitative research is suitable for examining the causal relationships between attending the training course and an increase in confidence and knowledge and a decrease in negative attitudes, whereas the qualitative research can provide a broader context for understanding of the data and come closer to the practice on the training course and behind the causal relationship found in the quantitative research [21].

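### The 250 per group is correctly calculated as the number to be analysed, but it is also the number randomised, so the stated 80% power for 0.19 holds only with about 98% follow-up

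*Protocol article*

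**What the plan says.** The Analysis outline gives the full set of inputs and the result. Alpha is 0.05, the target power is 80% and the SD is 0.75. The remaining input and the sample size are put as follows: "a smallest clinically relevant difference in means between the groups of 0.19 we would require 250 persons per group". Methods/Design sets the size of the trial as one "in which 500 participants will be allocated to either the intervention group or the control group". The outcome is collected by questionnaire at baseline and at six months.

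The article expects some non-response. Strengths and limitations says: "Previous studies have emphasized difficulties in obtaining adequate follow-up rates". It hopes that e-mail contact will limit this. Survey procedure sends the links "primarily to their work email-address, in order to avoid loss to follow-up", with reminders at both time points. The Analysis outline provides for covariates associated with attrition and for multiple imputation under a missing-at-random assumption. The article states no expected loss rate and no increase in the sample size to cover loss.

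**The concern.** A power calculation for a difference in means gives the number of participants whose outcome is observed. Here that number and the number allocated are the same, although the same article treats incomplete follow-up as a known difficulty. Every missing six-month questionnaire lowers the power below the stated figure, and the rounding from 246 to 250 covers only the first four losses per group.

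What is at stake is how a null or borderline result is read. The sponsor calls 0.19 the smallest difference that matters. If the trial is reported as having 80% power for 0.19 when it had, say, 71%, a non-significant result will be taken as stronger evidence against a worthwhile effect than it is.

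**Working it through.** **Inputs.** From the Analysis outline: alpha 0.05, power 0.80, SD 0.75, difference 0.19, 250 per group. From Methods/Design: 500 allocated in total. Two points are inferred. Allocation is taken as 1:1, because 500 in total matches 250 per group. The test is taken as two-sided, because a one-sided test would need only 193 per group and would not reproduce the plan's figure.

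**Step 1: reproduce the plan's figure.**
- Normal approximation: n = 2 × (1.960 + 0.842)² × (0.75/0.19)² = 244.6, so 245 per group.
- Exact two-sample t-test (noncentral t): 245.6, so 246 per group. Power is 79.9% at 245, 80.1% at 246 and 80.7% at 250.

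The plan's 250 is 246 rounded up. It contains no allowance for loss.

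**Step 2: how much loss the rounding absorbs.** 250 − 246 = 4 per group, and 4/250 = 1.6%. By the normal approximation it is 250 − 245 = 5, or 2.0%. So about 98% follow-up is needed.

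**Step 3: power and detectable difference under loss.** The article gives no rate, so the rates below are assumptions. Loss is taken as equal in both groups, with n analysed = 250 × (1 − loss). Power is for a difference of 0.19 by the t-test, without adjustment.

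| Assumed loss | Analysed per group | Power for 0.19 | Difference detectable with 80% power |
|---|---|---|---|
| 0% | 250 | 80.7% | 0.188 |
| 5% | 237.5 | 78.7% | 0.193 |
| 10% | 225 | 76.5% | 0.199 |
| 20% | 200 | 71.5% | 0.211 |
| 30% | 175 | 65.7% | 0.225 |

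The last column is also from the t-test. The normal approximation, 0.75 × √(2/n) × 2.802, gives 0.198 at 10% and 0.210 at 20%, which is no material difference.

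**Step 4: what baseline adjustment could recover.** With a baseline covariate correlated r with the outcome, the residual SD is 0.75 × √(1 − r²). At 20% loss (200 per group):
- r = 0.3: SD 0.715, power about 75%
- r = 0.43: SD 0.677, power about 80%
- r = 0.5: SD 0.650, power about 83%

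At 30% loss, r = 0.5 gives about 78%. The article gives no correlation, so these values of r are assumptions too.

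**The case against.** **The calculation is correct.** This stands. The inputs and the result agree, and a reader who took this point to mean that 250 is miscalculated would be wrong. What is missing is the condition of almost complete follow-up on which the 80% rests.

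**The shortfall may be trivial.** This stands for small losses. Passing the 2% mark only moves power from 80.1% to 79.9%, and at 5% loss it is still 78.7%. A reader might infer that the trial is seriously underpowered. The article does not support that, because it gives no loss rate and every larger shortfall above depends on an assumed one.

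**Multiple imputation handles the missing data.** This stands in part. Under missing at random, imputation addresses bias. If the baseline confidence items enter the imputation model, they bring back some information about missing follow-up scores. It does not in general make the data equivalent to 250 complete cases per group.

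**Baseline adjustment makes up the loss.** It might: Step 4 shows that a moderate correlation would restore 80% power at 20% loss. However, the stated calculation uses no correlation. The Analysis outline names allocation, its interaction with the vignette, and variables linked to attrition or baseline imbalance, if any. It does not fix the baseline confidence score as a covariate, so neither an adjusted nor an unadjusted figure can be assumed to describe the planned analysis.

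**The survey procedure guards against loss.** The plan has reminders, and the work address is only the primary one, so other addresses are not excluded. It would be a preference, not a finding, to ask for a different contact method. Nor do these measures come with an expected response rate that could support the power statement.

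**Conclusion.** The point holds as a missing condition on a correct calculation. The 80% power for 0.19 is a property of 246 analysed participants per group. The plan randomises 250 per group while itself anticipating attrition, so the statement is true only with about 98% response at six months. Unadjusted power falls by about 2 points at 5% loss (80.7% to 78.7%), about 4 points at 10% and about 9 points at 20%. In each case the difference detectable with 80% power exceeds the sponsor's own 0.19. These figures assume 1:1 allocation, a two-sided test, equal loss in the two groups and no gain from baseline covariates. The loss rates are not in the article.

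**What to change.** In the Analysis outline:
1. State that 80% power for a difference of 0.19 requires about 246 participants analysed per group.
2. State the expected six-month response and, for 500 randomised, give the power for 0.19 and the difference detectable with 80% power at that response. At 80% response, for example, these are 71.5% and 0.211 without adjustment.
3. If the sponsor wishes to rely on adjustment for baseline confidence, name that score as a fixed covariate in the primary model and state the correlation assumed, with the power at a lower value as well.

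The cost is a few sentences and a less favourable stated power. No additional participants are proposed. The baseline confidence items are already in the questionnaire, so item 3 needs no new data.

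### Baseline confidence, collected from everyone, enters the primary model only through an open-ended imbalance-or-attrition rule instead of as a fixed covariate, which forgoes most of its precision

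*Protocol article*

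**What the plan says.** Methods/Design sets two measurement times: "All the participants will answer a questionnaire at baseline and at six months follow-up". The section on instruments places the three confidence items that form the primary outcome in this questionnaire, so a baseline value of the primary outcome is planned for everyone.

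The Analysis outline then gives the model: "Continuous outcome measures will be analyzed using generalized linear models including treatment allocation, test of interaction term between allocation and the vignette used", and the same sentence goes on "as well as variables associated with attrition or baseline imbalances between the groups, if any". Two terms are therefore unconditional: allocation, and its interaction with the vignette. Everything else depends on what the data show. Dichotomous outcomes get logistic regression along the same lines, and missing data are to be multiply imputed.

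The sample size in the same section is introduced with "We calculated that with alpha = 0.05, a power of 0.8 and a standard deviation 0.75". The target is a mean difference of 0.19, and the resulting number is stated as "we would require 250 persons per group". The section does not say which quantity the SD describes, nor whether the analysed outcome is the six-month score or the change from baseline.

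**The concern.** The baseline value of a self-rated scale is usually among the best predictors of its later value. Including it removes the part of the follow-up variance that it explains, and corrects the estimate for whatever baseline difference chance has produced.

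The written rule chooses covariates on a different ground: whether the groups happen to differ, or whether the variable relates to dropout. In a randomised trial most baseline differences are small. The rule will therefore usually leave the score out, although its value for precision does not depend on imbalance.

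Three things are at stake: a wider confidence interval than the data need give, an estimate that carries any chance baseline difference not flagged, and a primary model whose content is settled only after the data are seen, by a criterion that is not stated.

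**Working it through.** **Inputs from the document (Analysis outline).** Alpha 0.05, power 0.80, SD 0.75, difference 0.19, 250 per group.

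**Assumptions, not in the document.** Two-sided test; 0.75 is the SD of the six-month score and also of the baseline score; baseline to follow-up correlation r = 0.3, 0.5 or 0.7; imbalance means p<0.05 on baseline confidence. The attrition trigger is not modelled. Calculations use the normal approximation.

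**Step 1: reproduce the plan's figure.** n per group = 2 × (1.960 + 0.842)² × 0.75² / 0.19² = 245 (246 with the noncentral t). At 250 per group, SE = 0.75 × √(2/250) = 0.0671, and power = Φ(0.19/0.0671 − 1.960) = 0.809. The stated 250 reproduces.

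**Step 2: baseline always included (ANCOVA).** Residual SD = 0.75 × √(1 − r²), used in place of 0.75 in the formulas above.

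**Step 3: change score.** SD of change = 0.75 × √(2(1 − r)).

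**Step 4: the written rule.** Simulation with 1,000,000 draws: use the adjusted test if the baseline difference has |z| > 1.96, otherwise the unadjusted test.

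| r | ANCOVA residual SD | Power, never adjusted | Power, written rule | Power, ANCOVA | Power, change score | n per group for 80% with ANCOVA | Type I error, written rule |
|---|---|---|---|---|---|---|---|
| 0.3 | 0.716 | 0.809 | 0.813 | 0.844 | 0.668 | 223 | 0.048 |
| 0.5 | 0.650 | 0.809 | 0.820 | 0.905 | 0.809 | 184 | 0.043 |
| 0.7 | 0.536 | 0.809 | 0.828 | 0.978 | 0.955 | 125 | 0.036 |

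Type I error is 0.050 for both always and never adjusting. Under randomisation this trigger fires in about 5% of trials, so the written rule behaves almost like no adjustment. At r = 0.5 it recovers (0.820 − 0.809)/(0.905 − 0.809) = 0.011/0.096, about 11% of the available gain in power.

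**Step 5: what an unflagged difference can do.** The largest baseline gap that escapes the flag is 1.96 × 0.0671 = 0.13. It shifts the unadjusted estimate by r × 0.13: 0.039, 0.066 or 0.092 at r = 0.3, 0.5 or 0.7. As a share of the 0.19 target this is 21%, 35% or 48%. These are upper limits for an unflagged gap; typical shifts are smaller.

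**The case against.** The strongest case on the other side has five parts.

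First, the plan does not omit baseline confidence. A reader who stops at the two fixed terms might infer that it does, but the rest of the sentence lets it in when it is imbalanced or related to attrition. This stands: the fault is conditional entry without a threshold, not exclusion, and dependence on chance differences applies mainly to those that go unflagged.

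Second, the primary outcome is worded as an increase, which may mean a change score. Baseline would then already be inside the outcome. The wording does not settle this. On that reading the remaining issue is change score versus ANCOVA, and the change score has lower power at each r in the table.

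Third, a reader might infer that the result is biased or the trial too small. Neither follows. Randomisation makes the unadjusted comparison unbiased on average with 5% type I error, the written rule as simulated errs on the conservative side, and the design meets its own power target.

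Fourth, the size of the gain rests on r and on what 0.75 measures. This stands. If 0.75 is already the SD of a change or of an adjusted residual, the table does not apply. Nor does the document give a dropout rate, so no figure for power after losses can be drawn from it.

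Fifth, a SAP that is not shown may list the covariates. It may, but the article does not merely leave the list open: it commits to a selection rule, and a SAP that fixed the baseline covariate would be replacing that rule.

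**Conclusion.** The point holds in this form: the outcome's own baseline value is measured in everyone but is made a conditional covariate, under a rule with no stated threshold. It is a matter of efficiency and prespecification, not of validity or sample size.

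Under the assumptions listed in the working, always including baseline would raise power at 250 per group from between 0.81 and 0.83 to between 0.84 and 0.98. The low end is a modest gain and the high end a large one; the document does not allow the range to be narrowed. That the written rule recovers little of the gain holds at all three correlations, given the p<0.05 reading of imbalance. A more liberal threshold would recover more, which is itself a reason not to leave it unstated.

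The change is worth making because the data are already planned for collection.

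**What to change.** Replace the conditional rule, as far as it concerns the outcome's own baseline, with a fixed one. Each continuous outcome is analysed as the six-month value on allocation, with the baseline value of the same outcome always included as a covariate, whether or not the groups differ on it. This also settles the follow-up versus change-score question. The planned test of the allocation-by-vignette interaction can stay.

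Include that baseline value in the imputation model. In the logistic models include it likewise, and note that the odds ratio is then conditional on baseline and is not the same quantity as the unadjusted one. State also which quantity the SD of 0.75 describes.

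The cost is a few lines in the analysis outline or the SAP, fixed before the outcome data are analysed. It needs no new data and no more participants.

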### Recruitment to the quantitative survey – criteria for inclusion

The MHFA training program was initially developed for the general public [13]. However, international experiences show that participants most often have been people who in their line of work are in contact with many different individuals [14]. We will try to replicate that in this study.

Hence, the study will recruit employees of 10 different workplaces, including public, private and non-governmental organizations (NGOs) sectors. Possible workplaces could be social services and job centers in different catchment areas of Denmark and telephone helplines in NGOs. A characteristic of the sample would then be its geographical diversity but with some occupational homogeneity.

The recruitment will be managed by an independent assistant at The Danish Mental Health Foundation. Contact will be established to leading officials at the different workplaces and NGOs, with whom the organization of participation at the given workplace will be arranged according to firm logistics. Participation will be presented as an opportunity for an education-based training course, relevant to the participants’ work life as well as private life. Participation will be voluntary and the training course will be held during work hours. Informed consent will be required and held in qualitative parts of the study.

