### The intervention – the MHFA training course

MHFA is a manualized, educational preventive strategy structured in a 12-hour course delivered over two days of training. The course will be carried out and managed by The Danish Mental Health Foundation.

MHFA is based on four training sessions of three hours each. The course gives an overview of the major categories of mental health disorders and crisis. The items presented include depression, anxiety, psychosis, and substance abuse. The crisis situations covered are; thoughts of suicide and suicidal behavior, self-harming behavior, panic attacks, reactions to trauma, acute psychosis, substance intoxication, and aggressive behavior. Participants are introduced to symptoms of the illness, possible risk factors, evidence-based treatment and where and how to get help [18]. The training will consist of a mix between knowledge-presentations and exercises, and a five-step action plan will be applied to each category of the mental health problems presented.

The action plan consists of a series of five steps, which include 1) Access risk of suicide or harm 2) Listen non-judgementally 3) Give reassurance and information 4) Encourage the person to get appropriate professional help, and 5) Encourage self-help strategies.

Further, the training involves cases and encourages the participants to bring in examples from their own experiences. All instructors are certified teachers and all experienced in working with people who have experienced mental health illness.

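### The trained arm is taught in group courses and the waitlist arm is not, but the sample size and the listed model terms treat all 500 participants as independent

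*Protocol article*

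**What the plan says.** Under Analysis outline, the sample size rests on four inputs: "We calculated that with alpha = 0.05, a power of 0.8 and a standard deviation 0.75", with "a smallest clinically relevant difference in means between the groups of 0.19", leading to 250 people per group. No ICC or design effect is mentioned.

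The same section describes the model: "Continuous outcome measures will be analyzed using generalized linear models including treatment allocation". The other listed terms are a test of the interaction between allocation and vignette, and variables related to attrition or baseline imbalance. Binary outcomes follow the same approach with logistic regression. Course is not listed, and neither is workplace.

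Three other sections describe how the data arise:

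- **The intervention – the MHFA training course:** teaching takes place in shared sessions over two days. "The training will consist of a mix between knowledge-presentations and exercises", and participants are encouraged to contribute cases of their own.
- **Participant observation:** two of the courses will be observed, so there are more than two or at least several. The observer will look at how behaviour and attitudes are negotiated among the participants.
- **Methods/Design:** the control group takes the course six months later, so it has no course groups during the comparison period.

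On workplaces, the recruitment section says "Hence, the study will recruit employees of 10 different workplaces". Strengths and limitations mentions a contamination risk between the arms "since they will sometimes work at the same workplace".

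**The concern.** People taught together share instructors, discussion, exercises and one another's examples. Their later confidence, knowledge and attitudes may therefore be more alike than those of people taught in different courses. The protocol's own qualitative plan treats participants as a social group in which knowledge and attitudes are formed.

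This dependence arises after allocation, so individual randomisation does not remove it. It also falls on one arm only. The variance of the intervention mean then contains a between-course component that a model for independent observations leaves out. The resulting p-values and confidence intervals are too optimistic, which in a superiority trial favours the intervention. The primary comparison is affected.

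**Working it through.** **Inputs from the protocol (Analysis outline):** difference 0.19, SD 0.75, alpha 0.05 (taken as two-sided), power 0.8, 250 per group.

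**Assumed inputs, not in the protocol:** course size *m* from 12 to 25, and course-specific ICC from 0.01 to 0.05.

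**1. Reproduce the stated figure.** For independent participants, n per arm = 2 × 0.75² × (1.960 + 0.842)² / 0.19² = 244.6, so 245 (246 with the t-test). A one-sided test would need 193, so the calculation was two-sided. At 250 per arm the standard error is 0.75 × √(2/250) = 0.0671, and power is Φ(0.19/0.0671 − 1.960) = 0.81. The figure is correct, but only under independence.

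**2. Add course clustering in the intervention arm only.** The design effect in that arm is DE = 1 + (m − 1) × ICC. The control arm keeps a design effect of 1, so the variance of the difference is multiplied by V = (DE + 1)/2. Then:

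- type I error of the planned test = 2 × [1 − Φ(1.960/√V)]
- large-sample power of a valid 5% test = Φ(0.19/(0.0671 × √V) − 1.960)

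| m | ICC | DE | V | Type I error, planned model | Power, valid test at 250 per arm |
|---|---|---|---|---|---|
| 12 | 0.01 | 1.11 | 1.055 | 0.056 | 0.79 |
| 25 | 0.02 | 1.48 | 1.24 | 0.078 | 0.72 |
| 25 | 0.05 | 2.20 | 1.60 | 0.121 | 0.61 |

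Simulation of the unadjusted comparison under the null (8000 runs, 25 per course) gave type I error 0.080 at ICC 0.02 and 0.123 at ICC 0.05, in agreement with the formula.

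**3. How much slack the design has.** Power stays at 0.80 only while 244.6 × V ≤ 250, that is while (m − 1) × ICC ≤ 2 × (250/244.6 − 1) = 0.044. This is an ICC of about 0.004 for courses of 12 (0.044/11) and about 0.002 for courses of 25 (0.044/24).

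**4. Check whether workplace does the same.** With individuals randomised in 10 workplaces of 50 and a workplace ICC of 0.02 to 0.10, simulated type I error was 0.042 to 0.049 and power 0.79 to 0.82. At ICC 0.05 the mean model standard error was 0.0669. The true SD of the estimate was 0.0645 if allocation is stratified by workplace and 0.0660 if not. Ignoring workplace therefore does not make the standard error too small.

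**5. Split the correlation between course and workplace.** Suppose each of the 10 workplaces supplies one course of 25 and 25 controls (an assumption), with total within-course ICC of 0.05. Let *c* be the course-specific part and *w* = 0.05 − *c* the workplace part, which cancels between the arms. In units of SD², the variance of the difference is c/10 + 0.95/250 + (1 − w)/250, against 2/250 = 0.008 in the planned model.

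| c | Variance | Ratio to 0.008 | Type I error |
|---|---|---|---|
| 0.05 | 0.0128 | 1.60 | 0.121 |
| 0.025 | 0.0102 | 1.275 | 0.083 |
| 0.01 | 0.00864 | 1.08 | 0.059 |
| 0 | 0.0076 | 0.95 | 0.044 |

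**The case against.** Four arguments can be made on the other side.

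- **The article is only an outline.** Random effects and variance estimation are often left to a statistical analysis plan, which is not shown, and listing some terms does not exclude others. This has some weight for the model. It does not answer the sample size, which is presented as complete and reproduces only under independence.
- **The size is unknown.** ICC and course size are not given, and the mildest case above is minor. The course is manualised and its instructors are certified, which may limit differences between courses. This stands: the plan cannot be said flatly to miss its alpha and power, only to miss them if outcomes correlate within a course.
- **Some within-course correlation may be harmless.** If courses follow workplaces, the workplace share also sits in the controls and cancels. This stands too, and makes 0.12 the upper end for ICC 0.05 and courses of 25.
- **The 10 workplaces are not a second source of error.** A reader might infer that nesting in workplaces also makes the standard errors too small, or that the remark that the arms "since they will sometimes work at the same workplace" means whole workplaces were allocated. The protocol supports neither. The Abstract and Methods/Design allocate 500 participants, and Randomization and blinding has the result passed on to each participant. Workplace effects then fall on both arms. The remark comes from a sentence about contamination and does not define the unit of allocation. It does fit loosely with individual allocation at about 50 people per workplace (500/10), where nearly every workplace would hold both arms. That justifies a clarification and nothing more.

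**Conclusion.** The point holds for courses. The sample size and the listed model terms do not match a design in which one arm is taught in groups and the other is not. The size is conditional: across the assumed range it runs from a minor distortion to a type I error more than twice nominal and a power shortfall of about 20 percentage points against the independence figure of 0.81. With only 5 participants per arm to spare (250 against 245), even a very small course-specific ICC takes power below 0.80.

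Two limits apply. The power figures use a large-sample formula. At 25 per course there are only about 10 trained courses (250/25), so power with small-sample degrees of freedom would be somewhat lower. In the other direction, any workplace correlation shared with controls reduces the effect. The 10 workplaces are not a cause of inflated type I error under the allocation that the protocol describes.

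**What to change.** 1. Record which course each trained participant attended. The organisation that runs the courses should be able to supply this, and it is easiest to capture while the courses run.
2. Analyse continuous outcomes with a linear mixed model that has a random course intercept in the intervention arm only and Satterthwaite degrees of freedom. SPSS, the named software, can fit this with its MIXED procedure. Use the logistic mixed counterpart for binary outcomes.
3. Include workplace as a fixed effect in both arms. The reason is precision, not control of type I error.
4. Restate the power for 250 per group with an explicit course size and ICC, and show a range. No additional enrolment is needed for this.
5. State that individuals are the unit of allocation, and bring the workplace remark under Strengths and limitations into line.

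The cost is a model change and one extra variable. Confidence intervals will be wider and the stated power lower, materially so if the course-specific ICC is near 0.05.
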